### Qualification of the Investigators

Researchers are required to have relevant qualifications or experience in conducting medical clinical research. Before the start of the study, the researchers will receive training to be familiar with the research plan, correctly master the inclusion and exclusion standards and scale evaluation methods, and fill in the Electronic Data Capture (EDC) in a standardized manner. In addition, psychological intervention training will be provided by mental health experts.

### Data Collection and Management

#### Data Entry and Modification

Data collection, entry, and modification will be conducted using the EDC and electronic Patient-Reported Outcome systems. The study will provide all participants with protocol-required laboratory and imaging tests at no cost, along with a fixed travel allowance for follow-up visits, to enhance patient adherence to follow-up visits. Participants who discontinue the study intervention or deviate from the protocol will be withdrawn from the study. Only the data from the last follow-up visit prior to withdrawal will be recorded. Two data managers will be responsible for data entry and verification. For questions in the EDC, the data manager will revise and confirm the data according to the original data of patients and the answers of researchers to ensure the overall data quality. Upon completion of data entry, consistency checks will be performed, and the database will be locked.

#### Missing Value Handling

Missing data will be handled according to the type and role of each variable. For missing diagnosis dates, original pathology records will be retrieved whenever possible. If the pathology report date is unavailable, the date of surgery will be used for imputation. If neither source can be obtained, the date of the patient’s first visit for ovarian cancer will be used, with the month imputed as July of that year and the day as the first day of the month. For baseline demographic and clinical characteristics, no imputation will be performed, and available data will be summarized descriptively. For safety outcomes, only observed AEs will be included in the analysis without imputation. For primary and secondary efficacy end points, missing follow-up data will be handled using multiple imputation under the missing at random assumption. The imputation model will include treatment group, baseline outcome values, and key prognostic covariates. Complete case analysis will be performed as a sensitivity analysis to assess the robustness of the primary findings.

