### Outcomes

#### Primary Outcome

The PNSC score is constructed based on the 4 most relevant symptoms (fatigue, sleep disturbance, distress, and sadness) from the MDASI-OC scale, in accordance with its usage guidelines [24]. Each symptom is rated on an 11-point scale, ranging from 0 (“no symptom”) to 10 (“the most severe imaginable”). The primary efficacy end point of this study is the difference in the PNSC remission rates between the intervention and control groups at 3 months after enrollment. Given that there is no universally accepted evaluation standard for the remission of this specific cluster, “remission” is defined in this protocol through expert consensus. A participant is classified as in “remission” if they meet at least one of the following PNSC-specific criteria: a ≥50% reduction in the total PNSC score relative to the baseline or an absolute PNSC score falling below the threshold of 4 after the intervention. While the primary comparison between the 2 groups will focus on the 3-month mark, longitudinal assessments will be conducted at baseline and at 1, 2, 3, 6, 9, and 12 months after enrollment to monitor symptom dynamics.

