### Data Analysis

#### Final Analysis

Data analyses will be performed using R (version 4.5.3 or later).

This study defines 2 analysis sets: the full analysis set (FAS) and the per-protocol set. The primary efficacy analysis will be conducted based on the FAS, following the intention-to-treat principle, including all eligible participants with available baseline data. The per-protocol set will be used for sensitivity analyses to assess the robustness of the results. Demographic and baseline characteristics will be summarized using the FAS. Safety outcomes will be summarized descriptively.

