#### Primary Outcome Analysis

The primary end point is the PNSC remission rate at 3 months after enrollment. The chi-square test will be used to analyze whether the difference in remission rates between the two groups is statistically significant. Meanwhile, the difference in remission rates between the experimental group and the control group, along with the 95% CI, will be calculated. In addition, to account for potential between-group heterogeneity, a binary logistic regression model will be performed, with group as the main independent variable and baseline PNSC scores included as covariates. Study center will be included as a fixed effect to account for potential between-center heterogeneity. In addition, longitudinal PNSC scores will be analyzed using the methods described below for repeated continuous outcomes.

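### The named imputation variables omit the month-1 and month-2 PNSC scores, and no planned analysis of the remission rate departs from missing at random

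*Protocol article*

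**What the plan says.** Under *Missing Value Handling*, for primary and secondary efficacy end points, "missing follow-up data will be handled using multiple imputation under the missing at random assumption". The model is then specified: "The imputation model will include treatment group, baseline outcome values, and key prognostic covariates". The prognostic covariates are not listed. The check on this is given in one sentence: "Complete case analysis will be performed as a sensitivity analysis to assess the robustness of the primary findings".

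Three other places bear on it:

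- *Primary Outcome* and Table 2: "longitudinal assessments will be conducted at baseline and at 1, 2, 3, 6, 9, and 12 months after enrollment". Two PNSC scores after baseline are therefore due before the month-3 end point. Remission is a function of that same score: "a ≥50% reduction in the total PNSC score relative to the baseline or an absolute PNSC score falling below the threshold of 4".
- *Randomization* stratifies by center, and *Primary Outcome Analysis* says of the logistic model: "Study center will be included as a fixed effect to account for potential between-center heterogeneity".
- *Final Analysis* adds a second sensitivity analysis: "The per-protocol set will be used for sensitivity analyses to assess the robustness of the results". *Primary Outcome Analysis* and *Secondary Outcome Analysis* add a linear mixed model of PNSC scores at all visits.

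*Sample Size* expects 20% dropout. *Data Entry and Modification* withdraws participants who stop the intervention or deviate, and records only the last visit before withdrawal.

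**The concern.** Missing at random is an assumption about what the imputation conditions on. If the model holds only arm and baseline information, a patient who left after two bad months is imputed as if she resembled everyone in her arm with the same baseline. The month-1 and month-2 scores can tell her apart. They measure the same construct as the end point, closer in time, and the stated model does not name them.

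Dropout that follows symptoms is foreseeable here, because withdrawal is tied to stopping treatment and to deviation. The imputed remission rates would then be wrong by an amount that depends on who leaves which arm. Complete case analysis uses almost the same information, so it would tend to agree with the imputed result and look like confirmation. No analysis of the remission rate asks what happens if missing at random fails.

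**Working it through.** **The plan's own figures.** With rates 0.40 and 0.10, margin 0.15, one-sided alpha 0.025 and power 0.80 (*Sample Size*):

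n = [0.40×0.60 + 0.10×0.90] × (1.960 + 0.842)² / (0.30 − 0.15)² = 0.33 × 7.849 / 0.0225 = 115.1, so 116 per group. Then 116/0.8 = 145. Both match. At the final 158 per group, 158 × 0.8 = 126 are evaluable.

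Scale for judging an error: the standard error of the difference at 126 per group is √(0.33/126) = 0.051, a 95% half-width of about 10 points. The assumed effect lies 30 − 15 = 15 points above the margin.

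**Simulation inputs.** From the documents: 40% v 10% remission under the protocol's definition, baseline mean PNSC of at least 4, and 20% dropout. Assumed, because the documents give nothing: score variances, a month-2 to month-3 correlation of 0.34, 0.69 or 0.88, and dropout log-odds rising by 1 per SD of the month-2 score. There were 400,000 patients per arm. Scores were imputed within arm and then dichotomized. With no missing data the difference was 29.7 to 30.2 points.

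Each cell gives, in points: imputation on arm and baseline / complete case / imputation with months 1 and 2 added.

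| Dropout pattern | r = 0.34 | r = 0.69 | r = 0.88 |
|---|---|---|---|
| Worse patients leave, both arms | 30.8 / 31.5 / 30.2 | 32.3 / 32.9 / 30.1 | 33.1 / 33.6 / 30.0 |
| Worse leave intervention only, control random | 31.0 / 32.2 / 29.9 | 33.4 / 34.3 / 29.9 | 34.5 / 35.3 / 29.8 |
| Worse leave control only, intervention random | 29.5 / 29.2 / 30.1 | 28.6 / 28.3 / 29.9 | 28.3 / 28.0 / 29.9 |
| Worse leave, 10% intervention, 30% control | 30.0 / 30.0 / 30.1 | 29.7 / 29.7 / 30.0 | 29.7 / 29.6 / 30.0 |
| Worse leave, 30% intervention, 10% control | 31.4 / 32.8 / 30.0 | 34.6 / 35.7 / 29.9 | 36.4 / 37.4 / 29.8 |
| Driven by unseen month-3 score, both arms | 33.6 / 34.2 / 33.4 | 33.7 / 34.1 / 31.9 | 33.7 / 34.1 / 30.7 |
| Driven by unseen month-3 score, intervention only | 35.1 / 36.2 / 34.8 | 35.0 / 35.9 / 32.3 | 35.2 / 35.9 / 30.7 |

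**Why the two planned analyses agree.** Take the first row at r = 0.69, intervention arm: true rate 40.0%, completers 44.5%, baseline-only imputation 43.5%. The leavers' true rate is (0.400 − 0.8×0.445)/0.2 = 22%. The rate imputed for them is (0.435 − 0.8×0.445)/0.2 = 39.5%. The imputation thus treats leavers almost like completers. The arm's error is 0.2 × (39.5 − 22) = 3.5 points. In control it is 11.2 − 10.0 = 1.2 points. The difference is off by 3.5 − 1.2 = 2.3 points.

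**Opposite directions by arm.** If worse patients leave the intervention arm and better ones leave control (r = 0.69), the baseline-only figure is 35.5 against 29.8, an error of +5.7. A separate simulation (158 per arm, 800 trials, month-2 to month-3 correlation 0.75, baseline to month-3 correlation 0.4) took the reverse pattern: 25.5 against 30.0, an error of −4.5. Complete case gave 24.9, and adding months 1 and 2 gave 29.9.

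**Milder settings.** At correlations 0.75 and 0.4, with worse patients leaving both arms and all dropout at month 3, the error is +2.4 at slope 1 and +1.3 at slope 0.5. With dropout spread over months 1 to 3, each step driven by the last score seen, it is +1.6 and +0.8. With a month-2 to month-3 correlation of 0.5 and spread dropout, it is +0.8 and +0.4.

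**Center.** No simulation included a center effect, so no size is attached to its absence.

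**The case against.** The strongest reply is that the sentence lists what the model will include and does not say only these. The prognostic covariates are undefined and could cover center. Secondary end points are imputed too, so interim visits may themselves be imputation targets, and a joint or chained model would then normally carry them as predictors. A fuller specification may also sit in an analysis plan that is not shown. This has weight: the omission is the plain reading, not a proven one. But the article does specify the model, and the only outcome values it names are baseline ones. An analyst following it as written could leave the interim scores out.

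Several stronger readings might be inferred, and the documents do not support them:

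- *Complete case is the only sensitivity analysis.* It is not; a per-protocol analysis is also planned. That set does not test missing at random, so complete case is only the sole analysis that changes the missing-data handling.
- *Any bias would go uncorrected and undetected.* The mixed model uses the interim scores under missing at random and might show a discrepancy. It estimates mean scores, however, not the remission rate.
- *Center is excluded.* It is unnamed. The chi-square test and the risk difference do not use it, and no effect of its absence has been shown.
- *Complete case rests on a stronger assumption than the imputation.* Not in general. The logistic model already adjusts for baseline PNSC and center, so fitting it to complete cases needs essentially the same assumption as baseline-only imputation.
- *The bias is large and has a known sign.* It can favor either arm or nearly cancel, and in many settings it is small beside the 10-point half-width.

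**Conclusion.** The point holds in limited form. As written, the imputation model relies on missing at random given arm and baseline information, although better predictors are collected. If dropout depends on the month-2 score at 20% overall, the error on a true 30-point difference runs from about 0 to roughly 5 points in either direction (5.7 in the most extreme opposite-direction run), and up to 6.6 points with 30% v 10% dropout. It is often 1 to 3 points. A 2- to 5-point error is about 0.4 to 1 standard error (0.02/0.051 to 0.05/0.051). That matters for the estimate and its interval but is unlikely by itself to reverse a true 30-point effect against a 15-point margin.

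Complete case stayed within about 1.4 points of the baseline-only imputation and erred the same way, so their agreement is weak evidence of robustness. Adding months 1 and 2 gave 29.8 to 30.2 points wherever dropout depended on the month-2 score. It left 30.7 to 34.8 where dropout depended on the unseen month-3 score. All sizes rest on assumed correlations, slopes and dropout timing.

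**What to change.** 1. In *Missing Value Handling*, state that the PNSC score is imputed separately by arm using the baseline, month-1 and month-2 scores and center, with remission derived from the imputed score. List the other prognostic covariates.
2. Add one sensitivity analysis of the remission difference that departs from missing at random: a delta-adjusted analysis carried to a tipping point. Interim scores alone do not protect against dropout that depends on the unseen month-3 score. Keep complete case, but do not present it as the test of robustness.
3. Reconcile *Data Entry and Modification*, which keeps only the last visit before withdrawal, with *Missing Value Handling*, *Final Analysis* and *Missing Data Analysis*, which promise imputation and inclusion of all randomized participants. Make clear that every PNSC score collected before withdrawal is retained for imputation. Read literally, the recording rule could discard a month-1 score that the improved model needs.

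The cost is revised wording, a little more programming and one extra analysis. No additional assessments are needed, and the article reports no recruitment as of April 2026, so the change can be made before any outcome data exist.

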#### Data Monitoring

The data monitoring committee for this experiment will be made up of 4 experts who are not involved in the research team. The committee will be in charge of external oversight, monitoring the study’s viability, data integrity, and safety. A risk-based monitoring approach will be adopted, primarily through random audits. Data with poor compliance or containing modifications in the EDC system will be subject to targeted review.

AEs must be documented in detail, appropriately managed, and tracked until resolution or stabilization. SAEs and unanticipated problems shall be reported in a timely manner to the Ethics Committee, the competent regulatory authority, the sponsor, and other relevant oversight bodies as required.

Study progress reports shall be submitted on schedule, including explanations for any AEs, subject withdrawals, and protocol deviations. The principal investigator will periodically conduct cumulative reviews of all AEs and, when necessary, convene investigator meetings to evaluate the risk-benefit profile of the study.

#### Data Preservation

All trial data, including documented participant eligibility, original signed informed consent forms, and detailed records of investigational product distribution and retrieval, will be maintained by the research team.

### Data Analysis

#### Final Analysis

Data analyses will be performed using R (version 4.5.3 or later).

This study defines 2 analysis sets: the full analysis set (FAS) and the per-protocol set. The primary efficacy analysis will be conducted based on the FAS, following the intention-to-treat principle, including all eligible participants with available baseline data. The per-protocol set will be used for sensitivity analyses to assess the robustness of the results. Demographic and baseline characteristics will be summarized using the FAS. Safety outcomes will be summarized descriptively.

#### Missing Data Analysis

To maintain the integrity of the intention-to-treat analysis, missing data for primary and secondary efficacy end points arising during follow-up will be handled using multiple imputation under the missing at random assumption. This ensures that all randomized participants are included in the final analysis, minimizing potential bias from attrition.

#### Descriptive Statistics

Continuous variables will be described as mean (SD) or median (IQR), as appropriate. Categorical variables will be presented as frequencies and percentages.

#### Primary Outcome Analysis

The primary end point is the PNSC remission rate at 3 months after enrollment. The chi-square test will be used to analyze whether the difference in remission rates between the two groups is statistically significant. Meanwhile, the difference in remission rates between the experimental group and the control group, along with the 95% CI, will be calculated. In addition, to account for potential between-group heterogeneity, a binary logistic regression model will be performed, with group as the main independent variable and baseline PNSC scores included as covariates. Study center will be included as a fixed effect to account for potential between-center heterogeneity. In addition, longitudinal PNSC scores will be analyzed using the methods described below for repeated continuous outcomes.

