### Sample Size

A superiority design is used for this study. Given the lack of a universally established remission standard for the PNSCs derived from the MDASI-OC scale, parameters are determined based on internal pilot data and expert consensus. The remission rate for the control group at 3 months is estimated at 10%. We posited an absolute increase of 30% in the intervention group, corresponding to an expected remission rate of 40%. To ensure clinical significance, a superiority margin (*M*) of 15% is prespecified and incorporated into the sample size formula. Assuming a one-sided significance level (α) of .025 and a statistical power (1-β) of .80, calculations performed via PASS software (version 15.0; Superiority by a Margin Tests for the Difference Between Two Proportions) yielded a required sample size of 116 participants per group. Accounting for an anticipated 20% dropout rate, a minimum of 145 participants per group is required. To further enhance the robustness of the findings and to accommodate potential variability in dropout rates or covariate adjustments, the final total sample size is determined to be 316 participants (158 per group). This ensures that the actual statistical power of the final analysis set remains consistently above 80%.

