#### Secondary Outcome Analysis

Linear mixed effects models will be used to analyze continuous variables with repeated measures (eg, scale scores at multiple time points). The models will include group, time, and their interaction as fixed effects; individual subject IDs and study centers will be incorporated as random effects.

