#### Survival Outcomes

One-year OS and PFS will be analyzed using the Kaplan-Meier method with log-rank tests. A Cox proportional hazards model will be used to estimate hazard ratios.

A one-sided *P* value of <.03 will be considered statistically significant.

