### Interim Analysis

One interim analysis is planned when approximately 50% of participants have completed the 3-month primary end point assessment. To control the overall one-sided type I error rate at 0.025, a group sequential approach based on the O’Brien-Fleming alpha-spending function will be applied, allocating one-sided nominal significance levels of 0.0026 and 0.0240 to the interim and final analyses, respectively.

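### Every stated significance level is one-sided, but the named chi-square and log-rank tests give direction-free P values as usually reported, and no passage says how the one-sided P is obtained

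*Protocol article*

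**What the plan says.** **Levels.** In the protocol article, Sample Size reads "Assuming a one-sided significance level (α) of .025 and a statistical power (1-β) of .80". Interim Analysis controls the overall one-sided error at 0.025, "allocating one-sided nominal significance levels of 0.0026 and 0.0240 to the interim and final analyses, respectively", and Formal Stopping Rules repeats the 0.0026 as one-sided. The sentence closing Survival Outcomes, and the abstract, say that a one-sided P below .03 "will be considered statistically significant".

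**Tests.** Primary Outcome Analysis says: "The chi-square test will be used to analyze whether the difference in remission rates between the two groups is statistically significant". It adds a 95% CI for the difference in remission rates and a logistic regression. Survival Outcomes says: "One-year OS and PFS will be analyzed using the Kaplan-Meier method with log-rank tests", with Cox hazard ratios. Secondary Outcome Analysis describes linear mixed models: "The models will include group, time, and their interaction as fixed effects".

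No section gives a direction for the chi-square or log-rank test, or says how a one-sided P value is derived from it. Sample Size calls the design superiority and builds a 15% margin into the calculation. Primary Outcome Analysis does not mention the margin.

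**The concern.** The article fixes both the test and the threshold, and the two are on different scales. A Pearson chi-square squares the difference, so its P value is two-sided in direction. The log-rank P that software normally prints is the same kind of quantity.

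If the chi-square P is halved when the intervention arm does better, the stated level holds. If the printed P is compared with the one-sided level, the test runs at half that level and loses power, and a difference favouring control could also satisfy the rule as worded. A borderline primary result would then be positive or negative according to a choice that the protocol leaves open.

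For survival, a rule read as one-sided toward benefit reports a result against the regimen only as not significant, although survival outcomes are a stated secondary objective.

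**Working it through.** **1. The plan's own sample size.** Inputs from Sample Size: control 10%, intervention 40%, margin 15%, one-sided 0.025, power 0.80, dropout 20%.

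n = [p1(1−p1) + p2(1−p2)] × (z_α + z_0.80)² / (difference − margin)²
= (0.09 + 0.24) × (1.960 + 0.842)² / (0.30 − 0.15)² = 115.1, so 116 per group; 116/0.80 = 145.

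Both stated figures reproduce. With one-sided 0.0125 the same formula gives 139.4, so 140. The trial is therefore sized for a one-sided test at 0.025, not for a two-sided P compared with 0.025.

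**2. The plan's group-sequential levels.** With one look at half the information, the two Z statistics have correlation √0.5. Critical values 2.794 (0.0026) and 1.977 (0.0240) give an overall one-sided error of 0.0250, as stated. Putting .03 at the final look in place of 0.0240 gives 0.0309.

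**3. Two readings of the chi-square at the final 0.0240.**
- Signed root, one-sided: critical z = 1.977, chi-square 3.91.
- Printed P below 0.0240: critical z = 2.257, chi-square 5.09. The one-sided level is 0.0240/2 = 0.012. With 0.0026 kept one-sided at the interim, the overall error is about 0.0134 against the stated 0.025.

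Results with z between 1.977 and 2.257 change verdict.

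**4. Worked example.** 158 per group, 16 control remissions (10.1%), uncorrected Pearson test, z = (p2 − p1)/√[p(1−p) × 2/158] with p pooled:

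| Intervention remissions | Difference | Pooled p | SE | z | One-sided P | Chi-square P |
|---|---|---|---|---|---|---|
| 29 (18.4%) | 13/158 = 0.082 | 45/316 = 0.142 | 0.0393 | 2.093 | .0182 | .0364 |
| 30 (19.0%) | 14/158 = 0.089 | 46/316 = 0.146 | 0.0397 | 2.233 | .0128 | .0255 |

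Both rows pass 0.0240 one-sided and fail it on the chi-square P. At .03 the counts that flip are 28 and 29; 30 is significant on both readings.

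**5. How often this would matter.** Exact binomial enumeration, single look at 0.0240, probability of significance in favour of the intervention. The true rates other than 10% versus 40% are assumptions, and 126 is 158 × 0.80 rounded.

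| True rates | Per group | One-sided reading | Chi-square P | Verdict differs |
|---|---|---|---|---|
| 10% v 10% | 158 | 2.4% | 1.2% | 1.2% |
| 10% v 20% | 158 | 70.7% | 60.3% | 10.4% |
| 10% v 20% | 126 | 60.5% | 49.6% | 10.9% |
| 10% v 25% | 158 | 94.7% | 90.9% | 3.8% |
| 10% v 25% | 126 | 89.0% | 82.7% | 6.3% |
| 10% v 40% | 126 or 158 | over 99.9% | over 99.9% | about 0.01% or less |

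**6. Survival.** A log-rank z of −2.3 (against the regimen) has a two-sided P of .021 and a one-sided P toward benefit of .989. Against .03 the first is significant and the second is not.

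**The case against.** **The tests can be made directional.** A two-group chi-square or log-rank test has one degree of freedom, so its signed root is a Z statistic with a one-sided P. The superiority design, the one-sided levels and a stopping rule for efficacy all point to benefit as the intended direction. This stands: the tests are compatible with a one-sided rule, and the defect is an unstated conversion. It does not remove the point, because the primary analysis as worded asks only whether the rates differ.

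**The practical effect is small.** At the planned rates it is negligible, and using the printed P errs on the conservative side, so type I error is not inflated. Disputed results are differences of about 8 to 9 points, below the 15% margin. All of this stands. However, a chi-square test of equal rates does not apply the margin, so such a result would still be called significant or not.

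**Readings that go too far.**
- A reader might infer that worse survival could never be called significant. That holds only if the rule is read as one-sided toward benefit. If the usual log-rank P is compared with .03, harm can be flagged, and the Cox hazard ratio shows direction either way.
- A reader might infer a multi-degree-of-freedom test of the group-by-time interaction. Secondary Outcome Analysis lists the interaction as a model term and names no test of it.
- A reader might take .03 as the single decision rule. The article also gives .025 and .0240, and these conflict.

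**Conclusion.** The point holds as a mismatch of scale between the stated levels and the named tests. Every level is one-sided, the primary and survival tests are direction-free as usually reported, and the link between them is not stated. If the chi-square P is compared with 0.0240, the one-sided level is 0.012 instead of 0.024, and about 10 percentage points of power are lost at a true 10% versus 20%. At 10% versus 40% nothing of substance changes.

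These figures assume the uncorrected Pearson test, a null difference of zero and no allowance for the interim look in the power figures. The one-sided reading is the one that matches the sample size. The point matters mainly for effects smaller than planned, and it is worth settling because the article reports no recruitment as of April 2026.

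**What to change.** - **Primary Outcome Analysis and Interim Analysis:** replace the chi-square P with a signed one-sided Z test of the remission rate, intervention minus control, judged at 0.0026 (interim) and 0.0240 (final). Give the confidence interval at the matching two-sided level: 1 − 2 × 0.0240 = 95.2% at the final analysis.
- **Null difference:** state whether the Z test is against zero or against the 15% margin used in Sample Size, and make the two sections agree. A test against zero with no comment would leave the analysis out of step with the sizing.
- **Abstract and Survival Outcomes:** remove the .03, so that 0.0240 is the only final level for the primary endpoint.
- **Survival and other secondary outcomes:** report two-sided P values and two-sided 95% CIs, so that an unfavourable result is visible.

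The cost is wording only, with no change to data collection from these edits. The small downside is that two-sided P values for survival and secondary outcomes are twice the one-sided values for a benefit. Reconciling the margin takes a decision by the trial team about which hypothesis is to be claimed.

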### Randomization

After registration and completion of the baseline assessment, eligible patients who provide written informed consent will be randomly assigned in a 1:1 ratio to either the intervention group or the control group. Randomization will be performed using a centralized system using center-stratified block randomization. An independent statistician, who is not involved in the trial implementation, will generate the allocation sequence. The randomization results will be encrypted and transmitted to an independent third party responsible for the allocation system, where they will be kept confidential until trial completion. The personnel responsible for participant recruitment and intervention delivery will remain blinded to the group assignments.

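### The trial is sized for superiority by a 15-point margin, but the named primary test is of zero difference and no success rule uses the margin

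*Protocol article*

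**What the plan says.** Protocol article, Sample Size: "A superiority design is used for this study". The assumed remission rates at 3 months are 10% in the control group and 40% in the intervention group. The section continues: "To ensure clinical significance, a superiority margin (*M*) of 15% is prespecified and incorporated into the sample size formula". The error rates are given as "Assuming a one-sided significance level (α) of .025 and a statistical power (1-β) of .80", and the calculation uses the PASS superiority-by-a-margin procedure for two proportions. The result is 116 per group, 145 after 20% dropout, and finally 158 per group (316 in total).

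Protocol article, Primary Outcome Analysis: "The chi-square test will be used to analyze whether the difference in remission rates between the two groups is statistically significant". The difference in rates is reported with a 95% CI. A logistic model with group, baseline PNSC score and study center is added.

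Protocol article, Interim Analysis and Formal Stopping Rules: one-sided nominal levels of 0.0026 (interim) and 0.0240 (final), with early stopping for efficacy if the interim statistic crosses the boundary. Neither section states the null hypothesis of that statistic.

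The 15-point margin appears only in the Sample Size section.

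**The concern.** The sample size answers one question (is the gain more than 15 points?) and the primary test answers another (is the gain more than zero?). A chi-square test of two proportions contains no margin, and the added logistic model compares the odds ratio with 1. The confidence interval could serve as a margin test, but no rule makes it one.

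What is at stake is the definition of a positive trial. A result such as 22% versus 10% would be positive under Primary Outcome Analysis and would fall short of the hypothesis in Sample Size. If the text is left as it is, the choice between the two readings could be made after the data are known. The same ambiguity reaches the decision to stop early for efficacy.

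**Working it through.** **Inputs.** From Sample Size: control rate 0.10, intervention rate 0.40, M = 0.15, one-sided α = 0.025, power 0.80, dropout 20%, 158 per group. From Interim Analysis: one-sided levels 0.0026 and 0.0240. Two group sizes are used below: 158, and 126 (158 × 0.80 = 126.4). The plan keeps all randomized participants through multiple imputation, so 126 is a complete-case scenario and 158 is the upper end.

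**1. Reproduce the plan's figure.** With unpooled variance,

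n = (z₀.₉₇₅ + z₀.₈₀)² × [p₁(1−p₁) + p₀(1−p₀)] / (p₁ − p₀ − M)²

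= (1.960 + 0.842)² × (0.24 + 0.09) / (0.30 − 0.15)² = 7.849 × 0.33 / 0.0225 = 115.1, so 116. Then 116 / 0.80 = 145. Both match.

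**2. Remove the margin.** With M = 0 the same formula gives 7.849 × 0.33 / 0.09 = 28.8, so 29 per group (32 with a pooled variance under the null). The margin therefore makes the trial about four times larger (115.1 / 28.8 = 4.0).

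**3. Smallest significant result, control near 10%, one-sided 0.025 (critical value 1.960).** For the chi-square test, Z = (p̂₁ − p̂₀) / √[2p̄(1−p̄)/n].

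- n = 126: 13 versus 25 remissions, p̄ = 38/252 = 0.151, Z = 0.0952 / 0.0451 = 2.11. With 24 instead of 25, Z = 1.958, just short. The threshold is 9.5 points (95% CI 0.8 to 18.3).
- n = 158: 16 versus 29, p̄ = 45/316 = 0.142, Z = 0.0823 / 0.0393 = 2.09. With 28, Z = 1.95. The threshold is 8.2 points (95% CI 0.6 to 15.9).

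The thresholds are the same at one-sided 0.0240. The margin test, Z = (p̂₁ − p̂₀ − 0.15) / √[(p̂₁(1−p̂₁) + p̂₀(1−p̂₀))/n], first succeeds at 13 versus 45 of 126 (25.4 points) or 16 versus 54 of 158 (24.1 points).

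**4. Probability of success, exact binomial enumeration, control 10%, one-sided 0.025.**

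| True difference | Chi-square, 126 / 158 per group | Margin test, 126 / 158 per group |
|---|---|---|
| 10 points | 61% / 71% | 0.1% / 0.1% |
| 15 points | 89% / 95% | 2.5% / 2.5% |

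**5. Power of the margin test at the final level 0.0240 (critical value 1.977), control 10%.** Power = Φ[(Δ − 0.15)/SE − 1.977].

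- Δ = 30 points: 83% (126) and 90% (158).
- Δ = 25 points: SE = √(0.3175/126) = 0.0502, and Φ(1.992 − 1.977) = 51%. With 158, SE = 0.0448, and Φ(2.231 − 1.977) = 60%.
- Δ = 20 points: 17% and 20%.

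**6. Interim, under an assumption.** If the boundary is applied to the chi-square statistic with 79 per group (half of 158), a true difference of 15 points crosses 0.0026 about 38% of the time. The margin test does so about 0.2% of the time.

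**The case against.** The strongest reply is that a zero-null test is valid for plain superiority: it controls the type I error, and the objectives speak only of evaluating efficacy and safety. The planned 95% CI also allows any reader to compare its lower limit with 15 points, which is the margin test at one-sided 0.025. Both points stand. They narrow the defect to a contradiction between sections and a missing decision rule. They do not remove it, because the protocol prespecifies the margin and then defines no success criterion that uses it. Nor can this be left to an analysis plan: the protocol already names the primary test, and a plan that applied the margin would depart from it.

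Four stronger readings are tempting and are not supported:

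- A reader might infer that the protocol declares effects below 15 points too small. It does not. It ties the margin to clinical significance, and the rest is inference.
- A reader might object that a chi-square test is two-sided. The plan fixes one-sided levels, and the signed root of the statistic is a one-sided Z test.
- A reader might fault the test for ignoring the center strata, given "Randomization will be performed using a centralized system using center-stratified block randomization". The same section adds a model with center and baseline score, and an unadjusted primary test with an adjusted supporting model is a common choice.
- A reader might say that the interim boundary uses the zero null. The text does not state its null, so the 38% above is conditional.

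**Conclusion.** The concern holds in this form: Sample Size and Primary Outcome Analysis rest on different null hypotheses, no rule links the confidence interval to 15 points, and the null at the interim is unspecified. As written, the trial can be declared positive on an observed gain of 8 to 10 points, and would be in 89% to 95% of repetitions if the true gain were exactly the margin. These figures assume 10% control remission, one-sided 0.025 and 126 to 158 per group. The thresholds and probabilities would shift with another control rate, but the mismatch does not depend on it. It should be resolved before enrollment, because it decides what counts as success.

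**What to change.** State one null hypothesis and one success rule, in the same terms, in Sample Size, Primary Outcome Analysis, Interim Analysis and Formal Stopping Rules.

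**To match the stated design:** test H0: difference ≤ 15 points at both looks. Claim success only if the lower confidence limit of the risk difference, at the allotted one-sided level (0.0026 interim, 0.0240 final), exceeds 15 points. Keep the zero-difference chi-square test as supportive. This changes wording only, and the planned 316 suffices at 40% versus 10%. The cost is a stricter criterion, with the lower power shown above if the true gain is 20 or 25 points. The sponsor should accept that knowingly.

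**Alternatively:** declare the zero null, rewrite the sample size rationale (the present 116 does not follow from that null), and make no claim of superiority by 15 points.

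A center-stratified or covariate-standardized risk difference is an optional refinement under either choice. The article reports no recruitment as of April 2026, so on that account the amendment would precede any outcome data.
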